## Abstract

**Background:**

Childhood obesity prevention is a public health priority. Children spend a large proportion of their waking time in school; therefore this is an appropriate setting to implement obesity prevention initiatives. Anecdotal reports suggest that implementing The Daily Mile in schools has had positive effects on childhood obesity, academic attainment and wellbeing. This trial aims to measure the effectiveness of The Daily Mile for improving health and wellbeing.

**Methods:**

This protocol describes a cluster randomised controlled trial (RCT) in 40 primary schools located in Birmingham, UK. Eligible participants are children in years 3 (aged 7–8) and 5 (aged 9–10). The study compares The Daily Mile (intervention) to usual practice (control) in relation to health and wellbeing. The Daily Mile intervention involves an additional 15 min of running or walking integrated into the school day, throughout a 12 month study period. The primary clinical outcome is body mass index (BMI) z-scores at 12 months following introduction of the intervention. The cost per Quality Adjusted Life Year (QALY) is the primary outcome of the economic evaluation. Secondary outcomes include wellbeing, physical fitness and teacher reported academic attainment.

**Discussion:**

This study is the first RCT investigating the clinical and cost-effectiveness of The Daily Mile. A range of outcomes will be measured to evaluate the broader wellbeing and academic benefits in addition to clinical outcomes typically measured in childhood obesity prevention trials. The intervention is simple and low-cost, therefore if the benefits are demonstrated it has enormous potential to influence future policy.

**Trial registration:**

ISRCTN: 12698269. Date protocol registered 27th October 2016.

**Electronic supplementary material:**

The online version of this article (10.1186/s12889-017-5019-8) contains supplementary material, which is available to authorized users.

## Background

Childhood obesity and overweight is a significant concern. In the 2015/2016 school year, 22.1% of children beginning primary school in England (reception, aged 4–5 years) were classified as overweight or obese. At primary school leaving age (year 6, aged 10–11 years) this figure was even higher, at 34.1% [1]. Not only does overweight at this age have immediate health implications such as increased risk of hypertension and insulin resistance [2], there is evidence that overweight children experience social rejection, discrimination and negative stereotyping [3]. The risk of these children becoming overweight adults is at least twice as high compared to normal weight children [4] and in the long-term, obesity and overweight are associated with premature death, increased risk of cardiovascular disease [5] and cancer [6].

Schools have been identified as effective settings to deliver interventions to prevent childhood obesity [7, 8]. The most recent Cochrane review [8] found a standardised mean change in Body Mass Index (BMI) of −0.14 (95% CI -0.21, −0.08) for interventions delivered in education settings alone. The effect increases when focusing on children aged between 6 and 12 years old only (−0.17, 95% CI -0.23 to −0.08), although caution is noted due to study heterogeneity and small sample sizes. A more recent review that focused only on interventions with a school-based component [7] found effectiveness of interventions delivered exclusively in schools had a mean difference in BMI z-score of −0.05 (95% CI -0.10, −0.01) or BMI -0.30 (95% CI -0.45, −0.15). The strength of evidence for school-based interventions was determined to be moderate.

Current physical activity guidelines recommend that children and young people between 5 and 18 years old should engage in at least 60 min of moderate to vigorous physical activity daily [9]. This is based upon evidence of the long-term benefits of physical activity, to include both physical and psychological well-being. The UK Government Childhood Obesity Strategy [10] recommends that of these 60 min, at least 30 min should be delivered in school time. Whilst active break times and physical education (PE) are opportunities for providing this volume of physical activity, issues with timetabling PE in a busy curriculum and ensuring play is active means achieving this daily target may be difficult. The Childhood Obesity Strategy [10] mentions The Daily Mile as an option to aid schools in delivering this volume of physical activity.

### The daily mile

The Daily Mile is an initiative developed and first implemented in a primary school in Stirling, Scotland in 2012. Initially designed to improve pupil’s fitness it is a simple and inclusive activity that increases children’s physical activity in school. In addition to improving physical health; further possible benefits include improved emotional wellbeing and academic achievement. The Daily Mile involves children doing an extra 15 min of activity by running or walking around a track within the school grounds. The 15 min reflects a distance of approximately one mile. Teachers can chose to do The Daily Mile at any time during the school day and in almost any weather, however it is not supposed to replace PE, break times or take place before or after school.

The Birmingham Daily Mile trial aims to conduct a robust evaluation of the effectiveness and cost-effectiveness of The Daily Mile in primary schools over 12 months. Despite anecdotal reports of its success in improving children’s fitness and wellbeing, as well as low rates of overweight in Stirling, there is currently no randomised controlled trial evidence supporting this. In addition, this study will assess the cost-effectiveness of the intervention. The Daily Mile may appear to incur no costs; however time and resources are incurred setting up and maintaining the intervention in the school day. The comparator is what the schools are routinely delivering to support health and wellbeing. This will enable a clear indication of the effect of introducing The Daily Mile to supplement existing initiatives.

### Trial aims and objectives

The aim of this pragmatic cluster RCT is to assess the clinical and cost-effectiveness of The Daily Mile in Birmingham primary schools for the purpose of improving health and wellbeing. The comparator intervention is usual practice (control arm), with schools receiving no additional physical activity intervention. Assessments of effectiveness will be conducted at 4 and 12 months following the initiation of the intervention. An economic evaluation will also be conducted to assess cost-effectiveness. The analysis will be conducted with and without implementation costs of the intervention. Qualitative methods will be used to explore the implementation of The Daily Mile and the measures used within the trial.

## Methods

### Trial design and overview

The Birmingham Daily Mile study is a pragmatic cluster RCT conducted in the large, multi-ethnic city of Birmingham in the UK. Primary schools are the unit of randomisation, with data collected at the cluster (school) and within cluster (individual children) level. Schools are randomised to either the intervention (Daily Mile) or control (usual practice) arm. To evaluate the effect of The Daily Mile, several clinical outcomes and quality of life/wellbeing measures are being collected. These are described later. Baseline measures were undertaken on all eligible participants prior to school randomisation (Spring 2017). Follow up measures will be undertaken 4 months post introduction of the intervention and again after 12 months. The study design is summarised in Fig. 1. Intervention schools will be expected to maintain implementation of The Daily Mile throughout the 12 month study period.

**Fig. 1 Fig1:**
[figure not shown]
Study design of The Birmingham Daily Mile trial

### Study setting and participant eligibility

All Birmingham, UK schools with at least 20 pupils in school years 3 (aged 7–8 years) and 5 (aged 9–10 years) were eligible for participation in the Birmingham Daily Mile study. Initially eligible schools from an ethnically and socio-economically diverse part of the city (Northfield) were invited to participate and schools that expressed an interest in the trial were enrolled. Subsequent pragmatic invitation of eligible schools from a wider area was used to reach the recruitment target of 40 schools whilst ensuring the final sample included schools that varied in terms of ethnic make-up and levels of deprivation. The recruitment of forty schools will provide a sample of approximately 2000 children at follow-up.

#### Exclusion criteria

Pupils that had a disability preventing them running or walking for 15 min and those that were unable to have their height and/or weight measured at baseline were excluded.

### Study recruitment

#### School recruitment process

Schools were approached by email, summarising the study and inviting them to attend a briefing event where the study would be described in detail. If unable to attend the briefing they could obtain further information and discuss participation with the study coordinator at another opportunity. Follow-up communication was by email and telephone.

#### Recruitment of study participants

Pupils from one class in years 3 and 5 at participating schools were invited to take part in study measurements. Parents or caregivers received a letter describing the study and measurements it involved. If they agreed for their child to participate they provided consent by returning a signed consent form (Additional file 1). In addition, children were required to verbally assent to participating at the time of measurement. All children in schools allocated to the intervention arm will take part in The Daily Mile intervention. However, data collection is confined to those consented for study measurements.

### Trial intervention

The Daily Mile aims to increase children’s physical activity by at least 15 min every day. Schools map out a route or track in their school grounds. Once a day at a time chosen by the teacher, the whole class run or walk as far as they can around the track in 15 min. Participants are not required to change their clothes although in adverse weather, coats may be necessary. Teachers are encouraged to participate and to undertake The Daily Mile with their class in all weathers as long as it is safe to do so. Schools are directed to The Daily Mile website for additional resources [11]. They are able to incorporate The Daily Mile into the curriculum if they wish. For example participants could count and record laps for maths. However, the intervention should not be used to replace PE or break times. The intervention will run for 12 months during term time.

#### Comparator

Schools allocated to the control arm do not receive any intervention and continue with their usual practice in regard to health and wellbeing activities. Currently the amount of physical activity that primary schools should provide is not mandated, however at least 2 h a week is recommended by the Office for Standards in Education, Children’s Services and Skills (OFSTED) [12]. More recently, the Childhood Obesity Strategy states that schools should provide 30 min of moderate to vigorous activity daily [10]. Schools in this arm are requested not to commence any new health or physical activity initiatives during the 12 month intervention period.

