## Discussion

Despite widespread uptake of The Daily Mile in the UK and its endorsement in UK policy documents, evidence for its success is currently only anecdotal. The Birmingham Daily Mile study will provide a robust evaluation of its impact on a variety of outcomes which include physical and, psychosocial health and academic attainment. Furthermore it will also evaluate its cost-effectiveness by including a within trial economic evaluation and decision analytic modelling. The Daily Mile is a simple and low-cost intervention which could provide a significant contribution to tackling childhood obesity. It therefore has great potential to impact health and education policy in the UK.

Childhood obesity is a complex issue with many contributing factors and no single solution [23]. The Daily Mile predominantly addresses one component, physical activity. There is no educational aspect to the intervention and no participation of family or caregivers outside of the school. Despite evidence suggesting that programmes involving both the home and school setting have most success in preventing childhood obesity [7], any contribution to reducing sedentary behaviour and perhaps encouraging additional activity outside of school is beneficial. Furthermore, by evaluating The Daily Mile in isolation and as it is currently being implemented will provide real-world evidence of its effect.

As a pragmatic study, a degree of variation in how well schools implement the study intervention is likely. Teachers are encouraged to use The Daily Mile as a tool for active learning or goal setting, for example, which may impact motivation or other contributors to implementation fidelity. Adherence to the recommended 15 min of activity daily may be variable and depend on other academic commitments or physical factors such as the weather. Teacher attitude may also affect whether children decide to continue doing activities similar to The Daily Mile outside of school such as on weekday evenings, at weekends or during school holidays. In addition, restricting the control arm schools from introducing new health initiatives for the duration of the study may also be ambitious. However, the large sample size, the participation of a diverse population and the inclusion of: cost-effectiveness; process evaluation and a variety of different outcomes are all strengths of this study which should provide a comprehensive assessment of The Daily Mile.

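### Only control schools are asked to start no new health initiatives, so if intervention schools add other effective programmes more often, the gain would be credited to The Daily Mile

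*Protocol article*

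**What the plan says.** The Comparator section defines the control arm in these words: "Schools allocated to the control arm do not receive any intervention and continue with their usual practice in regard to health and wellbeing activities". It then adds a condition: "Schools in this arm are requested not to commence any new health or physical activity initiatives during the 12 month intervention period". The Discussion confirms which arm this applies to and doubts that it will be met: "restricting the control arm schools from introducing new health initiatives for the duration of the study may also be ambitious".

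The Trial intervention section contains no corresponding request. Its related limit on intervention schools is: "However, the intervention should not be used to replace PE or break times".

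The Background (The daily mile) states the intended comparison: "The comparator is what the schools are routinely delivering to support health and wellbeing", followed by "This will enable a clear indication of the effect of introducing The Daily Mile to supplement existing initiatives". Trial aims and objectives calls the trial pragmatic and describes the comparator as usual practice without an additional physical activity intervention.

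The setting is one in which schools are being urged to do more. The Comparator section notes that "the Childhood Obesity Strategy states that schools should provide 30 min of moderate to vigorous activity daily".

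Schools are not blinded (Method of random allocation and blinding). The primary model contains the baseline value, trial arm, the three randomisation variables and a random effect for school, and is analysed by intention to treat (Planned statistical analysis). The school questionnaire asks about physical activity policies, other lifestyle initiatives and future plans (School level data). The article does not say when it is completed or how the answers enter the comparison of arms.

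**The concern.** The comparison the trial wants is existing practice plus The Daily Mile against existing practice. A request addressed to one arm only does not secure that. As written, control schools are discouraged from adding anything new in health or physical activity, while intervention schools remain free to. Schools know their allocation and are under national policy pressure to provide more activity, so new initiatives during the 12 months are plausible.

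If intervention schools add more of them, and they work, the arm difference contains the effect of The Daily Mile plus the effect of the extra programmes. The difference arises after randomisation, so neither the constrained randomisation nor the baseline covariates can correct it. In the economic evaluation the same excess would enter the incremental benefit, whereas the costing described in School level data is of the intervention and its implementation. Costs of unrelated new programmes might therefore not be set against it.

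**Working it through.** The article gives no figure for this bias, so there is nothing to reproduce directly. The check has two parts.

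**1. Requests by arm**

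| | Control schools | Intervention schools |
|---|---|---|
| Existing activities | Continue | Continue; The Daily Mile is not to replace PE or breaks |
| Other new health or activity initiatives | Asked not to start any | No request stated |
| Aware of allocation | Yes | Yes |
| Term for new initiatives in the primary model | None | None |

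The asymmetry comes from a rule that the article states twice for one arm. It is not inferred from the intervention section's silence alone.

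**2. Illustrative size**

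Inputs from the article:
- effect of school-only programmes: -0.05 BMI z-score, 95% CI -0.10 to -0.01 (Background);
- target difference 0.125, SD 1.3, ICC 0.04, baseline correlation 0.9, 50 children per school, 40 schools (Justification of sample size);
- significance at 5%, taken as two-sided because 95% CIs are reported.

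Assumptions, not in the article: 20 schools (1,000 children) per arm; 20-40% of intervention schools add such a programme; no control school does; the programme's effect adds fully to that of The Daily Mile.

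Bias = (uptake in intervention schools - uptake in control schools) x programme effect:
- 20% uptake: 0.20 x (-0.05) = -0.010, and 0.010/0.125 = 8% of the target;
- 40% uptake: 0.40 x (-0.05) = -0.020, and 0.020/0.125 = 16% of the target.

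Standard error of the arm difference = SD x sqrt[(1 - r²) x (1 + (m - 1) x ICC) x 2/n], with n children per arm
= 1.3 x sqrt[(1 - 0.81) x (1 + 49 x 0.04) x 2/1000]
= 1.3 x sqrt[0.19 x 2.96 x 0.002] = 0.0436.

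Probability of a significant result if The Daily Mile has no effect = Φ(b/SE - 1.96) + Φ(-b/SE - 1.96), where b is the absolute bias:
- b = 0.010: b/SE = 0.23; 0.0418 + 0.0143 = 5.6%;
- b = 0.020: b/SE = 0.46; 0.0666 + 0.0078 = 7.4%.

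At the limits of the quoted confidence interval:
- smallest: 0.20 x 0.01 = 0.002, rate 5.0%;
- largest: 0.40 x 0.10 = 0.040 (32% of the target), rate 15.1%.

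If uptake is equal in the two arms, the bias is zero.

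One caution on the standard error. With these inputs, power for 0.125 is Φ(0.125/0.0436 - 1.96) = 81.8%, not the stated figure of more than 90%. That is a separate matter. A smaller standard error would raise the false-positive rates above but leave the bias in BMI z-score unchanged.

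**The case against.** The strongest reply is that the comparator largely matches its own definition. The article defines it as what schools already deliver, with no additional physical activity intervention, and asks what The Daily Mile adds to existing initiatives. A control arm that carries on and adds nothing fits that. This stands in part. A reader might infer that the control request makes the comparator something other than usual practice, in contradiction of the text. The documents do not support that. Whether usual practice means practice at baseline or practice as it would have evolved is a design choice, and existing activities continue in either case.

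The request also has a sensible purpose. The Daily Mile is named in national policy and is already widely taken up, so controls might adopt it or something similar. Withdrawing the request would invite that contamination. This stands, and it is why the control request should be kept.

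The direction of any bias is not shown. It is a request and not a ban, the Discussion doubts compliance, and the Background mentions a crowded timetable. Schools already giving 15 minutes a day to The Daily Mile might add less, not more. A reader might infer that the trial is biased in favour of the intervention; the article has no uptake data from which to conclude that. A reader might also express the illustration as 20-40% of a -0.05 effect. That ratio only returns the assumed uptake, because the same -0.05 is in the numerator and the denominator.

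Finally, this is a condensed article. Intervention schools may have been told more than it reports, and the school questionnaire may already be due for repetition. Both are possible. Neither changes the fact that the restriction is twice described as applying to control schools, and that the Discussion treats it only as hard to achieve, not as a possible source of difference between the arms.

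**Conclusion.** The concern holds in a limited form. As written, the plan permits differential co-intervention: one arm is asked to refrain and the other, so far as the article says, is not. Any resulting difference would be attributed to The Daily Mile and could not be adjusted away with baseline data.

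The bias is conditional on intervention schools adding effective programmes more often than controls, and its size is unknown. The central illustration, -0.01 to -0.02 BMI z-score or roughly a quarter to a half of a standard error, is modest against the 0.125 target. It would weigh more if the true effect were near the article's own pooled -0.05. It rests on assumed uptake of 20-40% against none, full additivity, and equal arms of 20 schools. No comparable figure can be given for cost per QALY. This is a cheap improvement to make, not a flaw that undermines the trial.

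**What to change.** 1. Send intervention schools the same request, worded to cover new health or physical activity initiatives other than The Daily Mile. Keep the control request.
2. Use the existing school questionnaire at 12 months in both arms, if that is not already planned, and report new initiatives by arm beside the primary result and in the economic evaluation.
3. If the request stays control-only, describe the comparator in the conclusions and the economic evaluation as existing practice with no new initiatives, and name possible differential co-intervention as a limitation.

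The cost is one letter to the intervention schools (20 if allocation is equal) and possibly one repeat of an existing form. The drawback is a mild restriction placed on intervention schools after allocation, which makes the trial slightly less pragmatic. If that is unacceptable, items 2 and 3 can be done without it; they make any imbalance visible but do not prevent it.

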### Method of random allocation and blinding

Randomisation was carried out after consent was taken for the school, and after baseline observations were made, to ensure allocation concealment. Randomisation was conducted using a constrained randomisation approach [13]. To this end, the school size, the average BMI Z-score, and proportion of pupils eligible for free school meals, were used in a balancing algorithm to generate a balance statistic. A random allocation was chosen by an independent statistician from those allocations that exhibited the greatest degree of balance on these three characteristics. Due to the nature of the intervention and comparator, clusters and participants will not be blinded to their intervention allocation. Blinding will be maintained for researchers who undertake follow up measurements.

